### Outcomes measured

The primary outcome measures for the intervention will include:

•changes to therapy (initiations, changes, cessations) made following application of CARAT;

•difference in the proportion of patients receiving no therapy;

•overall difference in the proportion of patients receiving antithrombotic therapy;

•difference in the proportion of patients receiving warfarin therapy;

•difference in the proportion of patients experiencing adverse clinical outcomes (ALL events).

The secondary outcome measures will include:

•the sustainability of prescribed therapy over time, i.e., changes to antithrombotic therapy made during patient follow-up up to 12 months;

•incidence of any clotting (thromboembolism, stroke) events up to 12 months;

•incidence of any bleeding (minor or major hemorrhage) events up to 12 months.

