### Underutilization of preventative therapies

Although highly effective antithrombotic medicines, specifically warfarin, are significantly underutilized in practice [12-16]; data from local Australian practice shows that this is especially true in the target at-risk older population, even in the absence of apparent contraindications [12]. A fear of side effects underpins this [17,18] because antithrombotics inherently increase the potential for bleeding. Therapy, therefore, requires careful patient selection, close patient monitoring (via blood tests), and regular dosage adjustment. This is particularly true for warfarin, as pharmacological characteristics render its use more challenging in patients with multiple medical comorbidities and/or polypharmacy (e.g., elderly) [19].

Unfortunately, the inconvenience of therapy has led some clinicians to cite “old age” *per se* as a contraindication to treatment without further risk/benefit assessment, leading to the underutilization of warfarin. In older people the risk of stroke is high but so too may be the risk of medication misadventure [20], giving clinicians a platform to question whether initiating life-saving anti-coagulant therapy is done at the expense of causing potentially life-threatening side-effects.

In more recent times, clinicians have been awaiting the availability of alternative agents (so-called ‘novel’ oral anticoagulants - NOACs) to overcome some of these known challenges of warfarin therapy. Whilst the newer agents present viable, effective treatment alternatives (e.g., dabigatran, rivaroxaban, apixaban), they are not without their own inherent risks [21]. Furthermore, the cost-effectiveness of these agents must be carefully considered, before widespread use in the at-risk population can be supported. For this reason, decision-making regarding stroke prevention in AF is still largely focused on the selection of warfarin (anticoagulant) versus aspirin (antiplatelet) therapy, and has been highlighted again in the recent Australian Government Review into Anticoagulation Therapies for Atrial Fibrillation [22]. In any case, the expanding armamentarium of treatment options for stroke prevention in AF has added to the complexity of decision-making in this clinical context.

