### Data analysis

Computerized data analysis will employ SPSS (Statistical Package for the Social Sciences) Version 15. ANOVA will test for differences in continuous variables. The Chi-square test will examine differences in independent proportions. Kappa analysis will detect the level of agreement between prescribers’ clinical judgment and the CARAT output. Logistic regression analysis will identify predictors of clinical events (clotting versus bleeding), and selection of antithrombotic therapy, accounting for the use of the CARAT. Survival analysis will assess mortality rates in both arms. All analyses will necessarily be based on the ITT principle; standard imputation methods (e.g., last observation carried forward) will be used to estimate missing data (withdrawal, failure to start) and data analysed according to initial group (random) allocation. All analyses will be adjusted for the effects of clustering, and set at a significance (p) level of 0.05.

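### Five unranked primary outcomes, all tested at 0.05, leave no single test that decides whether the trial is positive; one duplicates another and one has no control-arm counterpart as worded

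*Protocol article*

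**What the plan says.** Under Outcomes measured, the protocol article opens its list with "The primary outcome measures for the intervention will include" and gives five items:

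1. "changes to therapy (initiations, changes, cessations) made following application of CARAT";
2. "difference in the proportion of patients receiving no therapy";
3. "overall difference in the proportion of patients receiving antithrombotic therapy";
4. the between-arm difference in warfarin use;
5. "difference in the proportion of patients experiencing adverse clinical outcomes (ALL events".

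No item is singled out as the main one, and nothing says whether one positive result is enough or all are needed. None of the five carries a time, whereas each secondary outcome is tied to follow-up of up to 12 months.

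The Data analysis section says: "All analyses will be adjusted for the effects of clustering, and set at a significance (p) level of 0.05".

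The Control Arm section has control GPs follow usual care. It offers them CARAT on 5 of their patients once the final 12-month follow-up is complete, to obtain feedback on the tool.

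**The concern.** A confirmatory trial needs to state in advance which result will count as success. Here several tests share the primary label and each is judged at 0.05. A favourable result on any one could be presented as the primary finding, and the trial-level false-positive rate is then above 5%.

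The list also has problems of content. Two items carry the same information. One is worded around use of a tool that only one arm has during the comparison. One appears to pool strokes with bleeds, although the background section warns that "antithrombotics inherently increase the potential for bleeding" and the section before it credits the same drugs with preventing stroke.

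**Working it through.** **1. The plan's own figure.** The Participants section gives a minimum of 25 GPs and 250 patients, from 35% on warfarin, upgrades of 15% to 23%, an ICC of 0.03 and 20% drop-out. Power is not stated, nor whether 250 is per arm or in total, so the figure cannot be reproduced uniquely. Taking two-sided 0.05, 80% power and absolute percentage points as assumptions:

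- Per arm, 35% v 50%: n = [1.96√(2×0.425×0.575) + 0.8416√(0.35×0.65 + 0.50×0.50)]² / 0.15² = 169.3, so 170. With 8 patients per GP left after drop-out, the design effect is 1 + 7×0.03 = 1.21: 170×1.21 → 206, and 206/0.8 → 258. With 10 per GP it is 1 + 9×0.03 = 1.27: 170×1.27 → 216, and 216/0.8 = 270.
- In total, 35% v 58% with continuity correction: 82 per arm; 82×1.21 → 100; 100/0.8 = 125; 2×125 = 250.

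Both readings can come close to or match 250, so the figure is not shown to be wrong. What matters here is that 35% on warfarin is the only base rate given.

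**2. How many distinct between-arm tests are there?**

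- Take no therapy to mean no antithrombotic therapy. If q is the proportion untreated, the proportion treated is 1 − q. The arm difference in one is d and in the other −d, with the same p-value. Five items become four.
- Controls do not use CARAT during the comparison, so changes made after its application have no control value as worded. Four become three: any antithrombotic, warfarin, pooled events. If the item is reworded to cover both arms, four remain.

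**3. Chance of at least one false-positive primary, each at 0.05, if any one suffices.** Formula for k independent tests: 1 − 0.95^k.

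| Tests | Independent | Bonferroni bound | Simulated |
|---|---|---|---|
| 3 | 14.3% | 15% | 13.9% |
| 4 | 18.5% | 20% | 18.3% |

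The simulation used 200,000 null trials with 157 effective patients per arm. Assumed rates were 19% on no therapy, 46% on aspirin and 35% on warfarin, with 36% changing therapy and 15% having an event. Changes and events were drawn independently of therapy, so real correlation could lower the rates further.

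**4. Pooled events.** The first three lines below are what the sections say; the last is an inference.

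- Study aim and objectives names strokes and bleeds as the clinical outcomes.
- Stroke prevention therapy says warfarin cuts stroke risk by about two-thirds and aspirin by about 20%.
- Underutilization of preventative therapies says these drugs raise the potential for bleeding.
- If CARAT increases treatment, strokes may fall while bleeds rise, and a single pooled proportion would not show which happened.

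**5. One primary compared with splitting alpha.** Take 250 per arm, 20% drop-out and 10 patients per GP: effective n = 200/1.27 = 157.5. For 35% v 50%, power = Φ[(0.15√157.5 − z√(2×0.425×0.575)) / √0.4775].

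- One primary at 0.05 (z = 1.960): 77%. With the 1.21 design effect it is 79%.
- Three tests at 0.0167 each (z = 2.394): 62%.
- Four tests at 0.0125 each (z = 2.498): 58%.

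**The case against.** Several counter-arguments have force.

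- **A multiplicity rule may sit in an analysis plan that is not shown.** That is fair, and the absence of such a rule is not the point. The point is what this document fixes: five co-listed primaries and one level for every analysis. An analysis plan would have to depart from that, and the duplicated and one-armed items would still need rewording.
- **The changes outcome is only badly worded.** This stands. Control GPs also review and select therapy, and current antithrombotic therapy is a patient data item in Table 1. A reader might infer that changes cannot be measured in controls; the documents do not support that. The item also omits the word difference, so it may be meant as a description of the intervention arm.
- **The timing can be inferred.** Partly right. Objective 1 refers to prescribing after the tool is applied, and later changes are a separate secondary outcome, so the therapy primaries plausibly refer to the period just after the index consultation. Since the Abstract has CARAT applied again at 12 months, the time should still be stated.
- **A null pooled result could hide a stroke–bleed split.** A reader might infer this, but clotting and bleeding are separate secondary outcomes, so a split would be reported. What the pooled outcome contains is itself inferred, and opposing effects are possible rather than established: CARAT can also recommend no therapy, and the Hypotheses section expects both strokes and bleeds to fall.
- **The sample size is not purely about warfarin.** Correct. The base rate is for warfarin, but the effect is stated as upgrades in therapy, which need not be warfarin alone.

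**Conclusion.** The point holds. The document defines no single test of success, one primary item is redundant, and one has no comparator as worded. Trial-level false-positive error is about 14% (three tests) to 18.5% (four tests), roughly three to four times the nominal 5%.

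This assumes that any one positive primary would suffice, that each is tested at 0.05, and that the tests are independent; correlation lowers it. If all primaries had to succeed, error would not be inflated but power would suffer; the document states neither rule.

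Two stronger readings should not be drawn. Five independent tests would give 1 − 0.95^5 = 22.6%, but a duplicated outcome adds no error. Nor does the point depend on power for stroke: stroke alone is not among the primaries, and the documents give no untreated stroke rate from which to calculate it. The pooled outcome is a problem of interpretation, not of concealment.

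**What to change.** - Declare one primary outcome: the proportion on warfarin, at one stated time after the index consultation, tested at 0.05. It is the outcome whose base rate the sample-size text supplies.
- Make the other outcomes secondary.
- Delete the no-therapy item as a duplicate.
- Define changes to therapy as therapy before compared with after the index consultation, in both arms.
- Move the pooled-events item out of the primaries, and report clotting and bleeding separately with confidence intervals.

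The cost is protocol wording and a registry update before recruitment, plus a check that the data forms record therapy before and after the index consultation in both arms. No extra patients or visits are needed. The downside is that a result on any other outcome can no longer be called primary. Keeping several primaries with a Bonferroni split would instead lower power for 35% v 50% from 77% to 62% (three tests) or 58% (four tests).

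Scoring or restricting the primary by CARAT indication is an optional design choice. Restriction may shrink the analysed sample when power in the full sample is only 77% to 79%, so it is not part of this fix.

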### Qualitative data collection and analysis

Qualitative data is integral to this study; it will triangulate the findings regarding the utility and refinement of CARAT for future sustainable implementation in general practice (previous data focused on CARAT’s utility in the acute care/hospital setting).

In-depth feedback will be obtained via individual face-to-face or telephone interviews. A semi-structured process will be adopted using a purpose-designed interview guide. Initially, 5 to 10 GPs in each arm will be interviewed until theme saturation is achieved. Each face-to-face interview will be digitally-recorded, transcribed verbatim, and then thematically analysed using inductive coding [37].

## Discussion

The need for tailored sustainable interventions to optimize the use of antithrombotic therapy for stroke prevention in at-risk patients is well documented [26], which will ultimately reduce the considerable burden of stroke suffered by individuals and the global community, on the background of an ageing population. In this study, a novel decision-support tool will be tested, to assist clinicians (specifically, GPs) in their decision-making.

Given the expansion of the treatment armamentarium following the development of the NOACs, the decision-making will necessarily become more complex, and will additionally be driven by the economic implications of the potentially widespread use of newer, more expensive therapies. This study specifically considers those therapies that have been historically available in the local practice arena, for which there is vast and robust evidence-base (i.e., warfarin, aspirin). However, the findings of this study will inform the need to integrate newer therapies, and their specific benefits and limitation, within decision-support tools. Separate to evaluating the impact of this tool as a targeted intervention, this study will additionally provide data on the absolute and relative risks of clinical outcomes (e.g., changes to therapy; stroke; bleeds; mortality) in an Australian cohort of older persons with AF, and identify predictors of these (e.g., risk factors, antithrombotics prescribed).

Our unique approach in this study addresses National Research Priorities in Preventative Health and targets major health issues in effective health care including an ageing population, burden of chronic illness, and translation of evidence into practice. A key feature of this study is that it targets the interface of patient care (general practice), addresses the at-risk population, and provides evidence for the impact of the intervention by evaluating related clinical outcomes. Its innovation lies in the application of a novel computerized antithrombotic risk assessment tool, developed by the researchers, to provide GPs not only with a screening instrument, but importantly a mechanism for comprehensive risk assessment that, for the first time, quantifies the risk versus benefit of antithrombotic therapy in individual patients. Eventually, the CARAT may be integrated into prescribing software, and/or other primary care services including Medication Review and Disease State Management rendering its application in practice highly sustainable.

## Abbreviations

AF: Atrial fibrillation; ANOVA: Analysis of variance; CARAT: Computerized antithrombotic risk assessment tool; GP: General practitioner; SF36: 36-Item Short-Form Health Survey; SPSS: Statistical package for the social sciences.
